### Intervention implementation

The interventions are initiated once all baseline data are collected, menu items are selected, menus are finalized, and trainings are completed; for each pair-matched restaurant, interventions start on the same day. After the new children’s menus are introduced (along with the healthy menu campaign in the menu-plus intervention condition), a KCRP intervention staff member conducts on-site support visits with each restaurant to monitor implementation and help restaurant managers/owners address any issues that may arise with the new children’s menus. These visits occur three times over the 10-week intervention for menu-only restaurants and weekly for menu-plus restaurants. Support visits consist of informal meetings lasting approximately 15 min that are guided by a set of open-ended questions and allow for discussion of any outstanding issues that need to be addressed. A KCRP intervention staff member monitors implementation to maximize implementation fidelity, addressing concerns with the manager/owner either immediately or soon after they are identified.

### Evaluation

#### Overview

A mixed-methods approach is used to evaluate the intervention on sales of healthy children’s menu items over an 18-week period, including during the 4-week baseline period. Primary outcomes are gross sales of healthy children’s menu items and units sold. Observations and interviews with a convenience sample of dining parties with children below the age of 18 years will determine changes in ordering behavior. Manager/owner interviews conducted during the baseline period and during the final 4 weeks of the 18-week data collection period (herein referred to as post-intervention period), and restaurant audits at baseline, mid-point of intervention and post-intervention periods will provide evidence of intervention impact on the manager/owner and restaurant environment. Our process evaluation includes an additional manager/owner interview once intervention activities are completed (i.e., exit interview). KCRP intervention staff visit the restaurants to capture implementation, dose delivered, dose received, and fidelity, and manager/owner and customer satisfaction with the intervention (see Table 1).

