#### Menu-plus intervention condition

Similar to a previous study [49], restaurants randomized to the menu-plus intervention condition are engaged in a more collaborative process of: (a) identifying healthy children’s menu items that may fit better with their existing adult and children’s menus (if available); (b) implementing a healthy children’s menu campaign that includes a printed children’s menu with copy and design elements that influence ordering behavior [50], a banner and table tents; and (c) kitchen staff and server training to prepare and promote the new healthy children’s menu items (see Table 1). Regarding the menu items, to maximize the sales of new children’s menu items, decisions about what items to include, their recipes, prices, etc., are made over three to four meetings with the restaurant manager/owner. It is important to get manager/owner buy-in to maximize implementation fidelity [51]. Regarding the campaign, the menus use copy and design elements that have been shown to capture consumers’ attention, including fun names and descriptions of the new menu items, placement of new menu items in specific locations on the menu, and boxing menu items and including pictures to draw attention to them (see Fig. 3) [50]. In short, the menu-plus intervention condition involves social and structural changes in the restaurants, with activities directed at the managers/owners, employees, and customers. Research-supported intervention activities geared toward development of the menus and campaign occur over several weeks immediately prior to the 10-week customer-directed activities.

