#### Employee trainings

In addition to the kitchen manager meetings, in the menu-plus intervention condition, kitchen staff receive a 15-min training introducing the KCRP project and the new children’s menu items in their proper portion and plating arrangements. Servers, bus-persons and hosts/hostesses also receive one 15-min introductory training, and a subset of servers, bus-persons, and hosts/hostesses participate in a second 15-min training a few weeks later. Using a script and slide presentation, KCRP intervention staff train the employees on the following topics: customer service and suggestive selling, interacting with dining parties with children, and promoting the new children’s menu items. Server training was identified as an important strategy for creating a stress-free environment, a factor identified as important to parents with young children when selecting a restaurant [42, 52]. These trainings occur during the development phase and prior to implementation of the new children’s menu and the healthy menu campaign. Optimal delivery of the trainings occurs in small groups; however, they can be delivered one-on-one. Trainings include opportunities for role playing and skill practice consistent with behavioral modification principles [53]. At the end of the introductory training session, employees are given a pocket guide to remind them of the key points of the training and provided strategies.

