After the orders are placed, a second trained KCRP evaluation staff member visits each table to conduct an immediate interview about ordering behavior and a second interview post-meal about consumption behavior. The former captures information on composition of the party, how frequently the dining party visits the restaurant, whether they are celebrating a special occasion, what was ordered and who placed the order for each child, and what influenced the ordering behavior (e.g., use of menus, other marketing materials, etc.), including whether the server suggested any menu items. Information on sharing of food and beverages is also captured. The post-meal interview captures information about how much was consumed, child satisfaction with the food, and adult satisfaction with the children’s menu items. To obtain consent for interviews, observed parties are handed an informational flyer and an informed consent/recruitment script is read by KCRP evaluation staff who then asks if they would be willing to participate. As soon as an adult member of the dining party agrees to participate, KCRP evaluation staff screens the dining party for eligibility: at least one adult 18 years of age or older and one child under the age of 18. If the dining party is eligible and agrees to participate, KCRP evaluation staff collects the post-order and then post-meal interview, collecting information for each child in the party. If the dining party refuses at any point during recruitment, the refusal is noted and no additional data are collected. If the dining party is ineligible, the party members are thanked for their time and ineligibility criteria are noted.

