#### Process evaluation

KCRP intervention staff members document resources needed to implement the new healthy children’s menu items. This includes information on what new foods and beverages the restaurant needs to purchase, and what new cooking and serving equipment are needed for each children’s menu item. KCRP staff monitor intervention implementation during check-in visits (three times during the 10-week intervention period in the menu-only restaurants and weekly in the menu-plus restaurants). In addition to assessing the overall restaurant environment (e.g., whether a special event is occurring, number of dining parties with children), the intervention staff member documents the quantity of KCRP children’s menus available, including any in use by dining parties with children, as well as banners and table tents in the menu-plus intervention condition. The intervention staff member also notes whether other children’s menu promotional activities are occurring (e.g., a special promotion) and/or whether any other healthy eating promotions are occurring.

Implementation of the trainings is assessed in three ways: **reach,** or the number of employees trained by gender and job title based on training sign-in sheets maintained by the intervention staff member; **dose delivered;** and **satisfaction.** Dose delivered is assessed both objectively in terms of the number of minutes of training time delivered to each restaurant by type of training, as well as subjectively, including trainer self-assessment of each training on: (a) the extent of content covered using an eight- to 13-item scale consistent with training content, (b) level of trainee engagement in each aspect of the training on a seven- to 12-item scale, and (c) conduciveness of the environment for the training using a four- to five-item scale. In terms of satisfaction, trainees are asked to complete a four-to-five item participant satisfaction survey at the end of training. In addition, satisfaction with all aspects of the intervention is assessed during the manager/owner exit interview (qualitatively) and post-intervention interview (quantitatively). Dining parties are asked about their satisfaction with the new main dishes, side dishes and beverages, as well as the taste of the food during the post-meal interview.

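### As written, intervention staff capture manager/owner satisfaction, after about 10 support visits in menu-plus against 3 in menu-only; for customers the article contradicts itself on who collects it

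*Protocol article*

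**What the plan says.** The protocol article distinguishes intervention staff from evaluation staff. Under Evaluation, Overview, it gives satisfaction to the first group: "KCRP intervention staff visit the restaurants to capture implementation, dose delivered, dose received, and fidelity, and manager/owner and customer satisfaction with the intervention".

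Intervention staff also deliver and support the programme. Under Intervention conditions they work with the manager/owner of every restaurant during a start-up of about six weeks. Under Employee trainings (menu-plus), "KCRP intervention staff train the employees on the following topics". Under Intervention implementation, "a KCRP intervention staff member conducts on-site support visits with each restaurant to monitor implementation and help restaurant managers/owners address any issues", and "These visits occur three times over the 10-week intervention for menu-only restaurants and weekly for menu-plus restaurants". In menu-plus, decisions about the menu items "are made over three to four meetings with the restaurant manager/owner".

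For managers, the Process evaluation section places satisfaction in the exit interview (qualitative) and the post-intervention interview (quantitative). Neither that section nor Secondary outcome evaluation says who conducts these interviews. Evaluation staff blind to condition are stated for the baseline measures only.

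For customers, Secondary outcome evaluation says that "a second trained KCRP evaluation staff member visits each table to conduct an immediate interview about ordering behavior and a second interview post-meal". It adds: "The post-meal interview captures information about how much was consumed, child satisfaction with the food, and adult satisfaction with the children". Process evaluation places the customer items in that same interview: "Dining parties are asked about their satisfaction with the new main dishes, side dishes and beverages".

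**The concern.** A manager who rates a programme to the team that helped build and run it may give a kinder answer than to someone else. If that courtesy were equal in both arms, it would raise the ratings but largely cancel in a comparison. Here contact with the team is greater in menu-plus by design, so it need not cancel. A higher menu-plus rating could then partly reflect who was asking.

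The post-intervention interview also carries the scales on perceived ability to promote healthy items, perceived barriers, and whether the programme improved the restaurant. If intervention staff conduct it, two things follow. Those scales share the exposure. In addition, the type of interviewer may differ between baseline and follow-up for the two scales meant to show change. With eight managers, four per arm, an interviewer effect could not be separated from an intervention effect afterwards.

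For customers the question is simpler: two parts of the article name different staff for the same information.

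**Working it through.** The plan gives no figure for this point, so the check is a comparison of sections plus simple counts.

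**1. Who asks managers about satisfaction**

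- Evaluation, Overview: intervention staff.
- Process evaluation: exit and post-intervention interviews, interviewer not named.
- Secondary outcome evaluation: timing and content of the manager interviews, interviewer not named.
- Restaurant selection section and Discussion: blinded evaluation staff, baseline only.

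The Overview sentence is therefore the only statement on who collects manager satisfaction, and nothing later replaces it.

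**2. Contact with intervention staff before the rating**

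- Timeline: 4 baseline weeks + 10 intervention weeks + 4 post-intervention weeks = 18 weeks. The exit interview falls within three weeks after the intervention period and the other interview in the post-intervention period. All scheduled support visits thus precede both.
- Support visits: menu-plus, weekly over 10 weeks = about 10; menu-only, 3. Ratio 10 / 3 = 3.3.
- Time, at about 15 minutes a visit: menu-plus 10 × 15 = 150 minutes; menu-only 3 × 15 = 45 minutes.
- Menu-plus planning meetings add 3 to 4, so 10 + 3 = 13 to 10 + 4 = 14 manager contacts.
- The number of planning meetings in menu-only is not given, although that arm also has a start-up period with intervention staff. No ratio of total contacts can be computed; the 3.3 applies to support visits alone.

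**3. Who asks customers about satisfaction**

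- Evaluation, Overview: intervention staff.
- Secondary outcome evaluation: evaluation staff, in the post-meal interview.
- Process evaluation: the same post-meal interview.

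These statements conflict. The support visits are meetings with managers/owners, so the visit ratio supplies no route to a difference in diners' answers between arms.

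**4. Interviews affected by the fix**

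8 restaurants × 2 interviews (exit and post-intervention) = 16.

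**The case against.** The strongest reply is that one overview sentence is being made to carry too much. It says what intervention staff visit to capture, not that they conduct the manager interviews, which neighbouring sentences describe without naming an interviewer. The detailed account of check-in visits lists the restaurant environment, menus, promotional materials and other promotions, not satisfaction. The baseline and post-intervention interviews are meant to be similar so that change can be assessed, and baseline measures were done by evaluation staff, so the same staff may well do the follow-up. The overview sentence is also already at odds with the detailed sections on customers, which weakens it as evidence on managers.

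This has force: evaluation staff may in fact conduct these interviews. But the article does not say so, and its one explicit statement says otherwise. This is a positive assignment, not a detail left to a fuller protocol, so the sentence needs correcting on either reading.

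A second reply is that importance is limited. Satisfaction is a process measure, and Planned analyses specifies no comparison of it between arms. That stands and lowers the weight of the point.

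A third is that closer collaboration with managers is part of menu-plus, so some goodwill is a genuine effect that a different interviewer would not remove. That stands too. The concern is only with the further courtesy produced by answering to the delivery team.

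A reader might also infer that customer ratings are biased differently by arm. The documents do not support this: the detailed sections give those items to evaluation staff, and the unequal visits are with managers.

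**Conclusion.** The point holds for managers/owners. As written, their satisfaction is captured by the staff group that helped set up and support the intervention, with about 10 support visits in menu-plus against 3 in menu-only. The ratings are therefore open to courtesy bias that may differ by arm. That such bias occurs is an inference from the design, and the documents give no basis for its size; any figure in scale points would be assumed.

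Two conditions apply. The conclusion rests on reading the overview sentence as governing the exit and post-intervention interviews. Extending it to the other manager scales requires, in addition, that the same staff conduct the post-intervention interview, which the article does not state.

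For customers the finding is only a contradiction to be reconciled. A reader might also infer that the trial's main result is at risk. It is not: the primary outcome is sales, in dollars and units, reported as weekly sales data and not as ratings given to an interviewer.

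The change is worth making because it is cheap and the bias cannot be removed once the ratings are collected.

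**What to change.** Amend the sentence in Evaluation, Overview so that intervention staff record implementation, dose and fidelity only. State under Secondary outcome evaluation and Process evaluation that evaluation staff not involved in delivery conduct the exit and post-intervention manager interviews in both arms. State that customer satisfaction is collected by evaluation staff in the post-meal interview, as the detailed sections already have it.

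If evaluation staff already conduct the manager interviews, the change is to wording only. Otherwise it moves 16 interviews to staff who already attend each restaurant every other week through the 18 weeks, so no new staff are needed. The gain is independence from delivery; it does not make the interviewers blind. The small downside is that the exit interviewer knows less of the restaurant's implementation history.

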#### Primary outcome evaluation

Sales in gross dollars and units sold are tracked for existing and new children’s menu items, as well as total gross food and beverage sales per week excluding alcohol. Weekly detailed sales data are collected for an 18-week period, starting during the 4-week baseline period. Managers/owners are given a sales data guide to help them prepare the data to maximize its utility for the study. In addition, reminder emails/phone calls are used to maximize getting the data in paper or electronic form. These data have the potential to yield information on calories sold in the form of new children’s menu items; however, funding limits prohibit us from evaluating the nutritional quality of existing children’s menu items.

#### Secondary outcome evaluation

Biweekly observations and interviews with dining parties occur in each restaurant over the 18-week period; 45 observations/interviews are planned for each restaurant. Dining parties are observed unobtrusively if they include at least one child who appears to be below the age of 18 and at least one adult. A trained KCRP evaluation staff member, acting as a server-in-training, captures the language of the interaction with the server, what is ordered for each child, and who places the order. All food and beverage orders for/by children are captured; however, if a child is sharing a meal with another child, the order is captured only once for/by the child who ordered. At the conclusion of the observation, the KCRP evaluation staff member also notes whether the server interacts with children directly, recommends food and/or beverage products off the children’s menu(s), or prompts use of any KCRP materials, and if the customers ask the server about KCRP or are observed looking at any of the KCRP materials.

After the orders are placed, a second trained KCRP evaluation staff member visits each table to conduct an immediate interview about ordering behavior and a second interview post-meal about consumption behavior. The former captures information on composition of the party, how frequently the dining party visits the restaurant, whether they are celebrating a special occasion, what was ordered and who placed the order for each child, and what influenced the ordering behavior (e.g., use of menus, other marketing materials, etc.), including whether the server suggested any menu items. Information on sharing of food and beverages is also captured. The post-meal interview captures information about how much was consumed, child satisfaction with the food, and adult satisfaction with the children’s menu items. To obtain consent for interviews, observed parties are handed an informational flyer and an informed consent/recruitment script is read by KCRP evaluation staff who then asks if they would be willing to participate. As soon as an adult member of the dining party agrees to participate, KCRP evaluation staff screens the dining party for eligibility: at least one adult 18 years of age or older and one child under the age of 18. If the dining party is eligible and agrees to participate, KCRP evaluation staff collects the post-order and then post-meal interview, collecting information for each child in the party. If the dining party refuses at any point during recruitment, the refusal is noted and no additional data are collected. If the dining party is ineligible, the party members are thanked for their time and ineligibility criteria are noted.

Managers/owners are interviewed three times over the course of their involvement: during the 4-week baseline period, within three weeks after the 10-week menu implementation period (exit interview), and during the 4-week post-intervention period. The baseline and post-intervention interviews are similar to assess changes in managers’/owners’ perceptions about the restaurant’s ability to promote healthy children’s menu items (six-item scale, 5-point Likert-type response options) and perceived barriers to implementation (nine-item scale, same response options). The baseline interview also includes an eight-item scale assessing the restaurant’s readiness to implement KCRP (same response options), as well as questions about the manager/owner such as his/her age, gender, race/ethnicity, years of education, employment history with the restaurant, and level of decision-making control. Several questions ask about the restaurant, such as the number of full- and part-time employees by job title. The post-intervention interview includes additional questions about managers’/owners’ perceptions of the various intervention components, including whether the KCRP intervention improved aspects of the restaurant, such as profitability and customer service (seven-item scale, same response options). Changes in the restaurant environment, including availability and promotion of foods and beverages, are captured at baseline, mid-intervention, and post-intervention with a restaurant audit tool adapted from the Nutrition Environment Measurement Survey for Restaurants (NEMS-R) [54] and the Children’s Menu Assessment (CMA) [55].

#### Process evaluation

KCRP intervention staff members document resources needed to implement the new healthy children’s menu items. This includes information on what new foods and beverages the restaurant needs to purchase, and what new cooking and serving equipment are needed for each children’s menu item. KCRP staff monitor intervention implementation during check-in visits (three times during the 10-week intervention period in the menu-only restaurants and weekly in the menu-plus restaurants). In addition to assessing the overall restaurant environment (e.g., whether a special event is occurring, number of dining parties with children), the intervention staff member documents the quantity of KCRP children’s menus available, including any in use by dining parties with children, as well as banners and table tents in the menu-plus intervention condition. The intervention staff member also notes whether other children’s menu promotional activities are occurring (e.g., a special promotion) and/or whether any other healthy eating promotions are occurring.

Implementation of the trainings is assessed in three ways: **reach,** or the number of employees trained by gender and job title based on training sign-in sheets maintained by the intervention staff member; **dose delivered;** and **satisfaction.** Dose delivered is assessed both objectively in terms of the number of minutes of training time delivered to each restaurant by type of training, as well as subjectively, including trainer self-assessment of each training on: (a) the extent of content covered using an eight- to 13-item scale consistent with training content, (b) level of trainee engagement in each aspect of the training on a seven- to 12-item scale, and (c) conduciveness of the environment for the training using a four- to five-item scale. In terms of satisfaction, trainees are asked to complete a four-to-five item participant satisfaction survey at the end of training. In addition, satisfaction with all aspects of the intervention is assessed during the manager/owner exit interview (qualitatively) and post-intervention interview (quantitatively). Dining parties are asked about their satisfaction with the new main dishes, side dishes and beverages, as well as the taste of the food during the post-meal interview.

